| --- | --- |

1. **Study design**

| **3.1**  **a. General description of the study design** | This research project will use the data infrastructure Extramural Leiden Academic Network (ELAN).  ELAN provides access to and the use of pseudonymized healthcare data from various cooperating partners such as healthcare data of general practitioners. The study period concedes 2014-2024.  ***Question***  Is antibiotic use associated with increased risk for urinary tract infection in adults?  Further explorations will be done to what extent the increased UTI risk of antibiotic use holds for:   - Different antibiotics or antibiotic classes - Men versus women - Post- versus Premenopausal women - Indication for antibiotic treatment (excluding UTI’s)   A self-controlled cases series (SCCS) design will be employed to establish the risk for developing an UTI within 3 months after antibiotic treatment compared to patients with an UTI who did not receive an antibiotic treatment. With the SCCS design, patients will be their own control.  The primary endpoint is risk of a UTI within 3 months after initiation of antibiotic treatment computed as an odds ratio.  An antibiotic treatment is defined as the exposure. An UTI between 2 weeks and 3 months after antibiotic treatment is defined as an event. The first 2 weeks after start of the treatment, patients are still somewhat protected by the antibiotic use against a new infection. And if a new antibiotic treatment is needed within 2 weeks after start of treatment, this is considered as treatment failure of the initial treatment.  Descriptive analysis will be performed for exposures, outcomes and covariables for the whole population of analysis and stratified by antibiotic use or not.  Multivariable logistic regression analysis will be performed to assess whether there is an association of antibiotic use with developing a UTI within 3 months after initiation of treatment. First a crude model will be used followed by confounder adjusted models. Confounders are season variability (Winter, spring, summer and autumn) and risk factors for UTI and selected based on theory or literature (Tj VanderWeele 2019). Risk factors are a history of an UTI, urine incontinence, urolithiasis, pregnancy, urine catheter, anatomical / functional abnormality urinary tract, immunocompromising comorbidities such as HIV/AIDS ,Type 2 Diabetes Mellitus.  **Subgroup analysis**  Subsequently, subgroup analysis will be performed to examine whether the association differs upon specific type of antibiotic treatment. For each subgroup, we will calculate an odds ratio for an UTI after antibiotic treatment. Subgroups are antibiotic(group)s, gender and age, type of infection and social determinants .  *Most used antibiotic(group)s in primary care*:   - Amoxicillin - Amoxicillin/clavulanic acid - Flucloxacillin - Tetracyclines - Macrolides - Fluoroquinolones - Trimethoprim - Co-trimoxazole - Fosfomycin - Nitrofurantoin   *Type of infection*   - All infections - UTI - non-UTI (all other infections)   *Gender and age*   - Men - Premenopausal women, defined as < 50 years of age - Postmenopausal women, defined as ≥ 50 years of age   *Social determinants*   - Socio-economic status (SES) - Migrant background |

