| --- | --- |
| **3.2**  **a. When will the study be conducted?**  **b. What is the intended end date of the study?** | The research will be performed as part of a MSc. Internship ([name]) in the period between February 2025 and June 2025.  Month 1 – Literature research, writing the introduction, first part of data preparation.  Month 2 – Writing the introduction and methodology, second part of data preparation.  Month 3 – Completing the introduction, methodology and data preparation, start of data analysis.  Month 4 – Completing the data analysis and writing the results.  Month 5 – Writing the report, focusing on the discussion.  The end date is July 2025. |
| **3.3**  **Does the study involve exclusively existing (patient) data (retrospective) and not data yet to be generated (prospective)?** | This study includes already existing data only, and is thus retrospective (see also 3.1). |
| **3.4**  **What type of data will be used for the research?** | Pseudonymized routine care patient data from GP practices participating in ELAN. |
| **3.5**  **If information from patient records is used: describe what type of information is involved.** | The dataset from ELAN contains data over a period of 10 years and includes:   - Number of all included patients in ELAN per year - All patients with an UTI   - ICPC code U70, U71, including subcodes   - Date of registration with GP office - Antibiotic prescriptions ATC J01 for all patients with an UTI   - Corresponding medical diagnosis with the antibiotic prescription by ICPC code   - Details on the antibiotic prescription (name of antibiotic, dose and duration) - Characteristics of included patients   - Year of birth   - Year of death   - Sex   - Referral to urologist for recurrent UTIs   - Risk factors for an UTI     - History of UTI ICPC code U70, U71     - Urine incontinence ICPC code U04     - Urolithiasis ICPC code U95     - Urine catheter ICPC code U28     - Anatomical / functional abnormality urinary tract ICPC code U85     - Type 2 Diabetes Mellitus ICPC code T90.02     - Prostate hypertrophy ICPC codes Y06, Y85     - Medication use for miction problems with ATC codes     - G04BD     - G04C     - Social economic status     - Migrant background |
| **3.6**  **To which time period do the data relate?** | The period between 2014 and 2024 |

1. **Data storage and privacy**

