| **4.10**  **If coding takes place: when will coding occur, by whom, and in what manner?** | Coding is done by STIZON and CBS |
| **4.11**  **Has a notification of the intended data processing been submitted via:**  <https://www.albinusnet.nl/weten-en-regelen/juridische-zaken/privacy/meldenverzamelenonderzoeksdata/>**?** | Yes |
| **4.12**  **If applicable: where will the coded data be stored, and who will have access to the coded data?**  **If applicable: where will the uncoded data be stored, and who will have access to the uncoded data?** | The coded data is stored, and a specific research folder assigned to the department disk (I: \) of PHEG. Only the researchers involved ([name] and [name]) and the PHEG data manager have access to this folder.  There is no storage of uncoded data. |
| **4.13**  **What technical and organizational measures have been taken to prevent loss, theft, or unauthorized use of the research data? For example, is a data safe being used?** | The data never physically leaves the research folder of the LUMC or the remote access CBS environment and see 4.12. |
| **4.14**  **By whom is the code key managed?** | STIZON. |
| **4.15**  **Will (research) data be shared with another institution(s) within the Netherlands and/or the EU?** | No. |
| **4.16**  **a. Will (research) data be shared with another institution/organization outside the EU?**  **b. Will the relevant patients be asked for consent to share their personal data with a country outside the EU?** | No.  Not applicable. |
| **4.17**  **How long will the (research) data be retained? If the data will be kept for longer or shorter than the standard retention period of 15 years, please explain why.** | After processing, the research data is returned to ELAN in accordance with the data transfer agreement. The LUMC department PHEG will keep the research data for 15 years. |

1. **Research population**

| **5.1**  **Inclusion criteria** | Adults patients 18 year and older with an acute UTI and registered at an GP office for a least 1 year |
| --- | --- |
| **5.2**  **Exclusion criteria** | Patients younger than 18 years of age.  Patients with antibiotic prophylaxes  UTIs are excluded as an event if   - During pregnancy - within 3 months after giving birth - within 1 year prior to an UTI (wash-our period) |

1. **Statistical analysis**

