| **6.1**  **a. Primary outcome**  **b. Secondary outcome** | ***Primary outcome***  What is the association of antibiotic use for any infection with risk for urinary tract infection in adults?   - Odds ratio for an UTI after antibiotic use in the preceding 3 months   - Per infection group, antibiotic for     - All infections     - An UTI     - An infection expect UTI’s   - Per antibiotic (group)   - Per patient group     - Men     - Women < 50 years of age     - Women ≥ 50 years of age   - Social determinants     - SES     - Migrant background   - Combinations of each subgroup   ***Secondary outcome***   - Hazard ratio for an UTI after antibiotic use in the preceding 3 months   - Per infection group, antibiotic for     - All infections     - UTI     - non-UTI   - Per antibiotic group   - Per patient group     - Men     - Women < 50 years of age     - Women ≥ 50 years of age   - Social determinants     - SES     - Migrant background   - Combination of each subgroup - Incidence of an UTI per month |
| --- | --- |
| **6.2**  **a. Statistical analysis primary outcome**    **b. Statistical analysis secondary outcome** | ***Primary outcome***  The Odds ratio for an UTI after antibiotic treatment the preceding 3 months will be calculated through a logistic regression model.  Risk factors and season variability are defined as confounders in this logistic regression model. Risk factors are a history of an UTI, urine incontinence, urolithiasis, pregnancy, urine catheter, anatomical / functional abnormality urinary tract and Type 2 Diabetes Mellitus. An Odds ratio for an UTI will be attributed to each confounder based on a critical literature appraisal.  ***Secondary outcome***  Cox proportional hazard regression models will be used to examine the associations between an UTI after antibiotic treatment the preceding 3 months.  Survival time (in days) was defined as the period between 14 days after the start of the antibiotic treatment and an UTI. The hazard ratio will be adjusted with the previous described confounders (see primary outcome).  The incidence of each UTI will be calculated for each month during 10 years to examine the season variability. |

1. **Appendices and references**

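### Risk time starts 14 days after treatment start whatever the recorded course length, which can lower the ratios for antibiotics with courses over 14 days, by an amount the protocol does not let one determine

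*Protocol*

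**What the plan says.** Protocol Section 3.1 explains the delay before risk time begins: "The first 2 weeks after start of the treatment, patients are still somewhat protected by the antibiotic use against a new infection". It adds a second reason, that a further antibiotic needed within those two weeks is regarded as failure of the initial treatment.

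Three statements place the window in time:

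- Primary endpoint, Section 3.1: "The primary endpoint is risk of a UTI within 3 months after initiation of antibiotic treatment computed as an odds ratio".
- Event definition, Section 3.1: "An UTI between 2 weeks and 3 months after antibiotic treatment is defined as an event". This sentence does not say whether it counts from the start or the end of treatment.
- Cox model, Section 6.2: "Survival time (in days) was defined as the period between 14 days after the start of the antibiotic treatment and an UTI".

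Section 3.5 lists among the variables to be extracted: "Details on the antibiotic prescription (name of antibiotic, dose and duration". Section 3.1 plans a separate estimate for each of ten antibiotics or antibiotic groups: "For each subgroup, we will calculate an odds ratio for an UTI after antibiotic treatment". Section 5.2 excludes "Patients with antibiotic prophylaxes" but sets no limit on the length of a treatment course.

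**The concern.** The first reason for the delay is that the antibiotic still protects. How long that lasts depends on how long the patient takes the drug, yet the rule is one constant counted from the start, the same for all ten antibiotic groups. Duration will be in the dataset, but none of the windows, confounder lists, subgroups or models in Sections 3.1, 6.1 and 6.2 refers to it.

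Followed as written, a course of D days with D above 14 contributes D − 14 on-drug days to the risk window. On the protocol's own reasoning those days carry a reduced risk, so they dilute the post-antibiotic effect that the study wants to measure. The main consequence is for the comparison between antibiotics. If course lengths differ between drugs, part of a difference in odds ratios may reflect duration and not the drug. Adjustment for the listed confounders would not remove this, because duration is not among them.

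**Working it through.** The protocol states no course lengths, effect size or sample size, so it contains no figure to reproduce. The following is an illustration with its assumptions marked.

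**Inputs**

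- Start of risk time: day 14 after start (Sections 3.1 and 6.2).
- End of window: 3 months after initiation (Section 3.1), taken as day 90. Window length W = 90 − 14 = 76 days.
- Course length D: not in the protocol; several values are shown.
- True off-drug ratio R = 1.5: assumed.
- On-drug ratio k = 0 (full protection) to 0.5 (half the reference risk): assumed.
- The rate is assumed constant within on-drug and within off-drug time.

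**Formula**

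On-drug share of the window: f = max(0, D − 14)/76. Observed ratio = f × k + (1 − f) × R.

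**If every course of a drug has length D**

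| D (days) | On-drug days in window | f | Ratio, k = 0 | Ratio, k = 0.5 |
|---|---|---|---|---|
| 14 or less | 0 | 0% | 1.50 | 1.50 |
| 21 | 7 | 9.2% | 69 × 1.5/76 = 1.36 | (3.5 + 103.5)/76 = 1.41 |
| 28 | 14 | 18.4% | 62 × 1.5/76 = 1.22 | (7 + 93)/76 = 1.32 |
| 42 | 28 | 36.8% | 48 × 1.5/76 = 0.95 | (14 + 72)/76 = 1.13 |

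Taking 3 months as 91 days (W = 77) gives 1.23 to 1.32 at 28 days and 0.95 to 1.14 at 42 days, so the choice is immaterial.

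**If only a share s of courses last 28 days and the rest at most 14 (k = 0)**

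Observed ratio = 1.5 × (1 − s × 14/76).

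- s = 1%: 1.497
- s = 5%: 1.486
- s = 10%: 1.472
- s = 50%: 1.362

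**Does the direction depend on k?** Yes. With k = 1 a 28-day course gives (14 + 93)/76 = 1.41. With k = 1.5 there is no shift, and above 1.5 the shift would be upward. The estimate falls only if on-drug risk is below post-drug risk.

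**Odds ratio against rate ratio.** Section 2.1 gives 117 UTIs per 1,000 registered women in a year. Over 77 days the reference risk is 1 − exp(−0.117 × 77/365) = 0.0244. With full protection and a 28-day course the exposed risk is 1 − exp(−0.117 × 1.5 × 63/365) = 0.0298, an odds ratio of 1.23. This agrees with the rate-ratio figure, so the approximation is adequate.

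**Short courses.** For D below 14 the rule drops 14 − D off-drug days: 13 after a single dose and 7 after a 7-day course. No on-drug time enters the window, but time since the last dose at window start still differs between drugs.

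**The case against.** The strongest reply is that an endpoint anchored on initiation is a legitimate choice. It matches the stated primary endpoint, it does not depend on recorded duration agreeing with actual intake, and the second reason for the two weeks (early re-treatment as failure) is itself tied to the start. This stands. The start-anchored analysis need not be abandoned; it answers a somewhat different question from the one about risk once protection has ended.

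It is also fair to say that the protocol describes patients only as partly protected, and that its background proposes microbiota disruption as the mechanism. On-drug risk could therefore lie above the 0 to 0.5 range for some drugs. The direction rests on the protocol's own premise, and its strength is assumed.

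Three stronger readings are tempting, and the document does not support them.

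- A reader might infer that the per-antibiotic odds ratios are in fact biased. That requires a material share of courses beyond 14 days, and no course length is given for any listed antibiotic.
- A reader might extend the arithmetic to courses of three months or more, where the whole window would be on drug and the real post-treatment period might fall into reference time. Nothing shows that such courses occur in the study population, and the prophylaxis exclusion removes some long-term use.
- A reader might claim that back-to-back prescriptions create the same problem. The protocol does not say whether a repeat prescription restarts the clock. If it does, the period after the last prescription is exposed time. Linking prescriptions into episodes can properly be left to an analysis plan.

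Nor can one say that duration will be used nowhere at all. It may appear in the planned description of exposures or in an analysis plan not seen here. What can be said is that no window or model stated in the protocol uses it.

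**Conclusion.** The point holds in a limited form. The fixed rule is explicit in two sections, its stated rationale depends on drug intake, and recorded duration does not enter it. For courses longer than 14 days this counts on-drug days as post-antibiotic risk time. That can lower the odds and hazard ratios of antibiotics with such courses and confuse course length with drug in the per-antibiotic comparison.

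The size cannot be determined from the protocol. It is nil for courses of 14 days or less, negligible where long courses are rare, and substantial only where they make up a large share of a drug's use. All figures rest on an assumed true ratio of 1.5 and an on-drug ratio of 0 to 0.5. A change is worthwhile because the variable is already being extracted, and because comparing antibiotics is a stated aim.

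**What to change.** Use the recorded duration to classify the days from treatment start to the later of day 14 and the recorded course end as a separate current-use period, counted as neither risk nor reference time. Start the risk window there, with the same length for every course (76 days if 3 months is taken as 90), and use the same point as the Cox time origin in Section 6.2. Apply this at least to the per-antibiotic analyses, or prespecify it as a sensitivity analysis beside the start-anchored result. On-drug share f is then zero by recorded duration, so in the illustration the assumed 1.5 is recovered at every course length. Also align the unanchored event definition in Section 3.1 with whichever anchor is chosen.

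The work is protocol wording and some data preparation. The costs are these:

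- Missing durations need a default, for example the median for that drug.
- Recorded duration may differ from actual intake.
- UTIs during long courses leave the main contrast.
- The window for long courses runs past 3 months from initiation: to day 28 + 76 = 104 for a 28-day course and day 42 + 76 = 118 for a 42-day course. The endpoint wording must allow for this.
- Time since last dose at window start will still differ among courses shorter than 14 days, so dependence on course length is reduced and not eliminated.

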| **2.1**  **Research question/objective(s) of the study** | The aim is to assess the association between antibiotic use and risk of subsequent urinary tract infections in adults.  ***Background***  Urinary tract infections (UTIs) encompass a spectrum of infectious syndromes that affect the urinary tract anywhere from the urethra to the kidneys and are one of the most common infections, particularly in primary care (Al Hawati, Blair & Larnard). In 2023, the UTI incidence in primary care was 20 cases per 1.000 registered men and 117 cases per 1.000 registered women (Nivel, 2024). Not only is the UTI incidence higher in women than men, it also increases with age (Ahmet et al., 2018).  Women are particularly susceptible due to the close proximity of the rectum to the urethra as well as a relatively short urethral length (Li & Leslie, 2023). It is reported that 50-60% of women have at least one UTI in their lifetime (Al Hawati, Blair & Larnard, 2023). Most UTI are caused by bacteria from the gut  (Worby et al. 2022).  Most patients with UTIs can be treated relatively simple with oral antibiotics, although treatment failure occurs. Around 20-30% of women with an initial UTI will experience a recurrent UTI within 3-4 months of initial infection (Foxman, 2003). Furthermore, some UTIs can become complicated through a pyelonephritis, prostatitis, and urosepsis, which are associated with morbidity and mortality (Sabih & Leslie, 2023).  A healthy vaginal microbiota is low-diverse and dominated by *Lactobacillus crispatus*.  Vaginal lactobacilli have been touted to prevent invasion of uropathogens, for instance by creating an acidic environment. Disruption of the vaginal ecosystem, causing an overgrowth of anaerobic bacteria or yeasts, increases the risk of vaginal infections such as sexually transmitted infections (Stapleton, 2016, Herthelius 1988). Conversely, treatment that restores a Lactobacillus-dominated microbiota is associated with lower risk of recurrent UTIs. Usage of antibiotics can alter the microbial community (Chee, Chew & Than, 2020).  In pre-menopausal women, factors related to sexual behaviour are major risk factors for UTIs. These include: having a new sexual partner, increased frequency of sexual intercourse as well as the use of spermicide-containing contraceptives (Hooton, 2001). Sexual behaviour is less firmly associated with UTIs in post-menopausal women, where age-, hormonal- and disease-related urogynaecology and immune factors play a more prominent role. An increased postvoid residual urine volume, the presence of bladder prolapse and urinary incontinence have been associated with UTIs (Athanasiou et al., 2010). Antibiotic use or treatment of asymptomatic bacteriuria has also been associated with the development of UTIs (Cai et al., 2014, Smith et al. 1997).  To date, only one small-scale study has been conducted on this subject, which indicated a potential correlation between antibiotic use and an elevated risk of urinary tract infections in pre-menopausal women (Smith et al. 1997). To our knowledge, there are no studies whether this also holds for postmenopausal women and men.  In this study, we would like to evaluate whether different antibiotics (either to treat UTI or other infections) are associated with increased risk of UTI in premenopausal women, postmenopausal women and men. If this association can be confirmed, the next would be to study effective preventive measure for an UTI. This would be highly beneficial, as urinary tract infections represent a significant burden for patients, while antibiotic use is also the major contributing factor to the development of antibiotic resistance. |

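### The pooled odds ratio for each antibiotic, and the single non-UTI stratum, cannot separate the drug from the infection it was given for, and no between-drug contrast within indication is planned

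*Protocol*

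**What the plan says.** Section 2.1 of the protocol sets the aim: "we would like to evaluate whether different antibiotics (either to treat UTI or other infections) are associated with increased risk of UTI". Section 3.1 lists antibiotics and antibiotic classes first among its further explorations and gives the purpose of the by-drug analysis: "subgroup analysis will be performed to examine whether the association differs upon specific type of antibiotic treatment". The estimate is fixed in the same section: "For each subgroup, we will calculate an odds ratio for an UTI after antibiotic treatment". Ten antibiotics or antibiotic groups are listed.

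The comparator in 3.1 is the absence of antibiotic treatment ("compared to patients with an UTI who did not receive an antibiotic treatment"), and the section adds: "With the SCCS design, patients will be their own control". No antibiotic is set against another.

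Section 6.1 lists the per-antibiotic odds ratio as an item of its own under the primary outcome, and the per-antibiotic hazard ratio under the secondary outcome. Neither item is restricted by indication. Type of infection is a separate subgroup with three levels: all infections, UTI, and "non-UTI (all other infections". Section 6.1 also lists "Combinations of each subgroup".

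The confounders in 3.1 and 6.2 are season and UTI risk factors. The infection that led to the course is not one of them. Section 3.5 shows that the dataset holds this item for each prescription: "Corresponding medical diagnosis with the antibiotic prescription by ICPC code".

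**The concern.** If the question is whether the association differs by antibiotic, the drug-specific ratios will be read side by side. That reading is sound only if the courses behind each ratio were given for comparable illness. The listed drugs include some used for UTI and some used for other infections, and a recent UTI itself raises the chance of another. A ratio against antibiotic-free time therefore carries the risk that comes with the infection as well as any effect of the drug.

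The self-controlled design does not remove this. It cancels patient traits that stay fixed over follow-up. The indication changes from course to course within a patient and coincides with the prescription.

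At stake is a conclusion that one antibiotic raises later UTI risk more than another when the two differ only in what they are prescribed for.

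**Working it through.** The protocol gives no sample size, power or expected effect, so there is no figure of its own to reproduce. The check has two parts.

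**1. What each planned row can separate (3.1, 6.1, 6.2)**

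- *Per antibiotic, all infections.* Reference: no antibiotic. The indication mix is whatever the drug is used for, and there is no adjustment for it. Drug and indication are mixed.
- *Per antibiotic, UTI courses only* (through the combinations in 6.1). The indication is broadly the same for every drug, so the UTI share no longer differs. No contrast or interaction between drugs is named.
- *Per antibiotic, non-UTI courses only* (also through the combinations). The UTI share is zero for every drug, but all other infections form one stratum. Drugs used for different non-UTI infections still differ by indication.

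**2. Possible scale for the pooled rows, assuming no drug has any effect**

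Inputs:

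- UTI incidence in women, 117 per 1,000 per year (2.1).
- Recurrence in women, 20-30% within 3-4 months (2.1).
- Share *u* of a drug's courses given for UTI: 0, 50 and 90%. The protocol gives no shares, so these are assumptions.

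Formulas:

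- Baseline 3-month risk: b = 1 - exp(-0.117 × 0.25) = 0.0288; odds 0.0297.
- 3-month risk after a UTI: r = 1 - (1 - R)^(3/m), with R = 0.20 or 0.30 and m = 3 or 4. Lowest: 1 - 0.80^(3/4) = 0.154. Highest: 0.300.
- Risk after a course of the drug: p = u·r + (1 - u)·b.
- Null odds ratio: [p/(1 - p)] / [b/(1 - b)].

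Results:

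| UTI share u | p, low to high | Null odds ratio |
|---|---|---|
| 0% | 0.029 | 1.0 |
| 50% | 0.091 to 0.164 | 3.4 to 6.6 |
| 90% | 0.142 to 0.273 | 5.6 to 12.6 |

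Sensitivity to the baseline: with b = 0.10 (assumed, because people in a UTI cohort have a higher background risk than registered women in general), the 90% drug has p = 0.149 to 0.280 and a null odds ratio of 1.57 to 3.50.

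Sensitivity to the wash-out: section 5.2 excludes some UTIs as events within a 1-year window, in wording that is unclear. If it removes every repeat UTI, r = 0. With b = 0.0288 the null odds ratio is then 0.49 at 50% and 0.10 at 90%.

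Within the UTI stratum u = 1 for every drug, and within the non-UTI stratum u = 0. By the same formula the null ratio is then equal across drugs inside each stratum. The spread above therefore belongs to the pooled rows alone. The protocol gives no figures from which to size the residual mixing inside the non-UTI stratum.

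**The case against.** The strongest reply is that the protocol already splits by indication. Type of infection is a subgroup, 6.1 crosses it with antibiotic for both the odds ratio and the hazard ratio, and 3.1 lists indication other than UTI as an exploration. This stands in large part. A reader might infer that every per-antibiotic ratio is pooled over indications, or that drugs can never be compared for the same infection. The documents do not support that: within the UTI stratum the ratios share a reference and broadly the same indication. The split does not reach the pooled rows, which remain listed in their own right, or the non-UTI infections, which the subgroup list does not divide further.

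The illustration can also be attacked. It is cross-sectional and unadjusted although history of UTI is a listed confounder. It takes a general-population baseline for a cohort of UTI patients, and it counts three full months although events count only from two weeks. All of this is fair. The figures show possible scale, not a forecast of a self-controlled estimate.

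A further reply is that the by-drug questions are exploratory and each drug is set against none. A reader might infer that the study aims to rank antibiotics, but ranking is not a stated aim. Nor do the documents show that drug differences would reflect the infection instead of the drug, only that the pooled ratios cannot tell the two apart. The stated wish to see whether the association differs by antibiotic is nonetheless a comparison between drugs.

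Finally, a named contrast or interaction test may be left to a SAP. That is true of the test. The comparator, the adjustment set and the infection strata, however, are fixed in the protocol.

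**Conclusion.** The point holds in a limited form. The pooled per-antibiotic odds and hazard ratios cannot be separated from the infection treated, and the single non-UTI stratum leaves the same problem among drugs used for different non-UTI infections. Self-control and the listed confounders do not remove it.

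For the pooled rows, indication alone could move the odds ratio of an inert drug from 1.0 to as much as 12.6 at 90% UTI use. At an assumed 10% baseline the 90% figure is about 1.6-3.5, and it falls to about 0.10 if the wash-out removes repeat UTIs. These values rest on assumed UTI shares, the protocol's figures for women and a cross-sectional calculation. Both size and direction depend on how 5.2 is read. The mixing within the non-UTI stratum cannot be sized from the document. The versus-none comparison for the overall question is not challenged by this point.

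**What to change.** In sections 3.1 and 6.1:

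1. Keep the versus-none odds and hazard ratios for the overall question.
2. Label the pooled per-antibiotic ratios descriptive, and state that they will not be used to conclude that antibiotics differ.
3. Add between-drug contrasts within indication groups built from the linked ICPC diagnosis, for example airway, skin and UTI. Within each group, estimate the ratio of each drug's effect to that of the most-prescribed drug in the group, in the same self-controlled model and over the same risk window, so that the control for fixed patient traits is kept. Base conclusions about drug differences on these contrasts.

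Drug name and linked diagnosis are already extracted (3.5), so the cost is protocol wording and extra analysis, with no new data. The downside is wider intervals, some cells below the 10-unit output minimum in 4.9, and no usable comparator for an antibiotic that is used almost alone for one infection.
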